## Statistical criteria of termination of trial

No interim analysis is foreseen.

## Planned Analyses

### Primary Analysis

The primary outcome parameter will be the comparison of incidence of SSI rates before and after the intervention. An interrupted time series design will be used, including 36 data points (based on about 20 surgeries per data point) before and about 36 data points (based on about 20 surgeries per data point) after the intervention. Interrupted time series allow to assess influences of trends and random fluctuations over time. We will include type of surgery, the NNIS-risk score (composed of ASA-score, wound contamination and duration of the surgery), as well as patient age as covariates. Covariates are included to adjust for chance imbalances between baseline and post intervention groups.

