## Determination of Sample Size

Sample size: The incidence of SSI after abdominal surgery in the department for Visceral Surgery and Medicine is 20%. The aim is to detect a reduction of the overall incidence rate of SSI from 20% to 14% after a follow-up of 30 days. We defined the level of significance at 5% and power of 80%, assuming normal approximation to binomial distribution requires 484 surgeries in each cell, thus 968 patients overall. In the ongoing StOP?-study we have a drop out and study refusal rate of maximal 20%. Thus, a total of 1160 participants (580 per arm) need to be included.

Duration: The average number of laparotomies from 8:00 AM to 5:30 PM from Monday to Friday per year are 720. The study schedule includes first 9 months in the control (baseline: 2^nd^ arm of the STOP? Study) and then 9 months in the intervention group.

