### Secondary Analyses

Interrupted time series analyses will also be performed for the secondary outcome parameters (mortality and complication rate), including the same covariates as for the primary outcome parameter.

There are many known influences on SSI^15^. Given the extensive inclusion criteria (basically all surgeries except those where SSI was the reason for surgery), we expect a similar risk profile before and after the intervention. The Swissnoso protocol includes assessing ASA-score, duration of surgery, wound contamination class and type of surgery. This information allows to calculate the NNIS-risk score for each surgery.

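### Section 10.4.1 analyses points of about 20 surgeries without saying at which level the covariates enter; if they enter as point averages, power is lost against the same model fitted per surgery

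*Protocol*

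**What the plan says.** The unit of the primary analysis is set in section 10.4.1: "An interrupted time series design will be used, including 36 data points (based on about 20 surgeries per data point) before" the change of team. The second period is laid out in the same way, with "about 36 data points (based on about 20 surgeries per data point) after the intervention". The reason given for a time series is: "Interrupted time series allow to assess influences of trends and random fluctuations over time". The form of the time terms is not given.

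For adjustment, the same section plans to "include type of surgery, the NNIS-risk score (composed of ASA-score, wound contamination and duration of the surgery), as well as patient age as" adjusters, and gives their purpose: "Covariates are included to adjust for chance imbalances between baseline and post intervention groups". It does not say whether they enter per surgery or as summaries of a point.

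Section 10.4.2 plans the same kind of analysis for mortality and complications. Of the recorded risk data it says: "This information allows to calculate the NNIS-risk score for each surgery". The SSI outcome is likewise assessed for each patient (sections 5.1 and 9.1.1).

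The sizing in section 10.2 counts individual surgeries: "assuming normal approximation to binomial distribution requires 484 surgeries in each cell, thus 968 patients overall".

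**The concern.** A regression whose observations are points can use covariates only as point summaries: the share of each operation type, the mean NNIS score and the mean age. The number of observations is then the number of points. The covariates are there to remove imbalance between the two periods. Estimating their coefficients from a few dozen points does this imprecisely and widens the interval for the closure-team effect. The same data, covariates and time terms can be fitted per surgery, where over a thousand observations carry the same few coefficients. At stake is precision in the primary comparison.

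**Working it through.** **1. The plan's own figure.** Section 10.2 gives 20% vs 14%, 5% significance and 80% power. With the pooled-variance normal approximation,

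n = [z_α √(2·0.17·0.83) + z_β √(0.20·0.80 + 0.14·0.86)]² / 0.06².

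- One-sided 5%: (1.645·0.5312 + 0.842·0.5295)² / 0.0036 = 484, the printed figure.
- Two-sided 5%: (1.960·0.5312 + 0.842·0.5295)² / 0.0036 = 615.

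The hypotheses in section 10.1 are worded two-sided, so the comparisons below use two-sided 5%. The calculation contains no data points, covariates or time terms.

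**2. Number of points.** As printed, 36 × 20 = 720 surgeries per period, or 72 points in all. The target of 580 per arm gives 580/20 = 29 points per period (58 in all). Nine months at 720 per year gives 540, or 27 per period (54 in all). The range is therefore 54 to 72 observations.

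**3. Why power is lost.** Assume 10 surgery types, with NNIS and age linear: 9 + 1 + 1 = 11 covariate coefficients. With chance imbalance only, adjusting for k covariates in N observations inflates the variance of the step term by about (N − 3)/(N − 3 − k).

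- Points, N = 58: 55/44 = 1.25, so the standard error rises by √1.25 = 1.118.
- Surgeries, N = 1160: 1157/1146 = 1.01.

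Unadjusted, the effect divided by its standard error is 0.06/√(0.2804/580) = 2.73, and power is Φ(2.73 − 1.96) ≈ 78%. On points it is 2.73/1.118 = 2.44, and power is Φ(2.44 − 1.96) ≈ 68%. This predicts a loss of about 9 to 10 points before any allowance for the t distribution.

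**4. Simulation.** There were 1,500 runs per scenario in the main grid and 2,000 in the extra ones. A logistic regression per surgery was compared with the same terms fitted to point totals and point-mean covariates, by grouped logit and by least squares on proportions. The protocol does not give the number of types, the covariate strength (SD of the linear predictor) or the time terms, so these are assumed. There was no true trend and no autocorrelation.

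| Points per period × size | Types, SD | Time terms | Per surgery | Points (logit / least squares) | Loss |
|---|---|---|---|---|---|
| 29 × 20 | 5, 0.5 | none | 79.7% | 73.7 / 72.7% | 6.0 / 7.0 |
| 29 × 20 | 10, 0.5 | none | 79.1% | 68.7 / 67.7% | 10.4 / 11.4 |
| 29 × 20 | 10, 1.0 | none | 83.3% | 70.3 / 72.2% | 13.0 / 11.1 |
| 36 × 20 | 5, 0.5 | none | 86.9% | 83.0 / 82.4% | 3.9 / 4.5 |
| 36 × 20 | 3, 0.3 | none | 85.6% | 83.8 / 83.4% | 1.8 / 2.2 |
| 29 × 20 | 15, 1.2 | none | 84.6% | 65.8 / 69.1% | 18.8 / 15.5 |
| 29 × 20 | 5, 0.5 | trend | 29.4% | 26.1 / 26.3% | 3.3 / 3.1 |
| 29 × 20 | 10, 1.0 | trend | 32.5% | 21.7 / 23.7% | 10.8 / 8.8 |
| 36 × 16 | 5, 0.5 | trend | 26.6% | 24.3 / 25.3% | 2.3 / 1.3 |
| 36 × 20 | 10, 1.0 | trend + slope change | 36.8% | 27.0 / 30.7% | 9.8 / 6.1 |

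Over the main grid (5 or 10 types, SD 0.5 or 1.0) the losses were:

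- Without trend terms: 3.9 to 13.0 points with points of 20, and down to 3.0 when 580 surgeries are spread over 36 points.
- With a trend: 1.3 to 10.8 points.
- With trend and slope change: 1.6 to 10.6 points.

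The Monte Carlo error of a single power near 75% is √(0.75·0.25/1500) = 1.1 points, so the smallest losses are little more than noise.

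**5. Validity.** With independent surgeries, null rejection was 3 to 7% for both approaches (600 runs per cell), so the cost is precision.

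**The case against.** **The level of adjustment is inferred.** A reader might conclude that the protocol averages the covariates within points. It does not say so. Per-surgery covariates with the point as time index, or risk-adjusted point rates, also fit the text, and a statistical analysis plan could settle this. That stands, and the power loss is therefore conditional. What remains is that the protocol itself fixes the analysis on points, and a better unit is available at almost no cost.

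**A plain logistic regression could be worse.** The series is meant to capture random fluctuation over time, and a fit that treats surgeries as independent drops it. With an assumed between-point SD of 0.3 on the logit scale (29 points of 20), such a fit rejected a true null in 7 to 10% of runs, against 5% for least squares on points. At SD 0.5 it was 13 to 15% against 5%. This stands and changes the remedy. Clustering the errors by data point brought rejection to about 4 to 8.5% and still kept about 4 to 10 points of power over the point-level fit. The upper end is still above 5%, hence the small-sample correction. With an assumed lag-1 correlation of 0.5 between points, both the independent per-surgery fit and the point-level fit were inflated.

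**The mechanism can be misread.** It is tempting to say that averages vary little and so explain little. That is wrong: averaging 20 independent surgeries shrinks covariate and outcome variance by the same factor. The loss comes from the number of coefficients relative to the number of points, so it depends on how surgery type is coded.

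**It does not rescue the time series.** This is correct. At 580 per arm a trend term takes per-surgery power from about 77 to 84% down to about 27 to 33%, and the unit of analysis does not recover that.

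**Conclusion.** The point holds conditionally. If the covariates enter as point averages, the planned regression has less power than the same model per surgery in every scenario run, with two different point-level models. The size is about 1 to 19 percentage points. The top of the range needs 15 types, strong covariates and no trend term; with a trend term that case gave at most 13.3. No single figure can be read from the documents, because the number of types, the covariate strength and the time terms are all assumed.

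Two stronger readings are not supported. The documents do not show that the planned test is invalid, since under independence its false-positive rate was near 5%. Nor do they show that a per-surgery fit would bring a trend model to the power stated in section 10.2. This is an improvement worth making, not a fatal flaw.

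**What to change.** In section 10.4.1, specify a segmented logistic regression on individual surgeries:

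- outcome SSI yes/no, a term for the intervention period, and the same time terms as planned;
- type of surgery, NNIS score and age entered per surgery;
- a random effect for the data point (about 20 consecutive surgeries), or cluster-robust standard errors by data point with a small-sample correction, so that fluctuation over time stays in the error term;
- a check of residual autocorrelation between points.

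Keep the points for the run chart. If per-surgery adjustment was intended all along, the same paragraph makes it explicit.

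Use the same form in section 10.4.2 where event counts allow. At an assumed 30-day mortality of 2 to 5%, between 0.95²⁰ = 36% and 0.98²⁰ = 67% of points of 20 would contain no death, so a series of proportions suits that outcome poorly.

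The cost is one paragraph and somewhat more complex modelling, with no new patients or data. If there is real variation between points, part of the power gain is given up.

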14.2 Patience Information (D,F,E,I)…………………………………………………………………………..27

14.3 General Consent (D,F,E,I)……………………………………………………………………………….32

Study synopsis

| Sponsor / Sponsor-Investigator | [name], Department of Visceral Surgery and Medicine, Inselspital, Bern University hospital University of Bern, 3010 Bern |
| --- | --- |
| Study Title: | Impact of a specialised wound-closing team on surgical site infections: A  prospective observational clinical trial |
| Short Title/Study ID: | CLOT trial |
| Protocol Version and Date: | Version: 1 Date: 18.01.2017 |
| Trial registration: | ClinicalTrials.gov (as soon as ethical approval is obtained) |
| Study category and Rationale | Category A: Observational study without relation to the use of drugs or medical devices. The risk for the participant is minimal and the study provides no additional strain to the participant. |
| Background and Rationale: | Surgical site infection is a frequent complication after abdominal surgery. The wound closure is done at the end of the procedure when the attention of the entire team may be affected because of tiredness and reduced attention of the surgical team.  With this study we aim to test if an exchange of the surgical team by a specialised wound closure team may reduce the impact of surgical site infection. |
| Objective(s): | To assess the influence of a specialised wound closure team on surgical site infections. |
| Outcome(s): | Primary outcome: Incidence of surgical site infections 30 days postoperatively.  Secondary outcome: mortality at 30 days, fascial dehiscence at 30 days postoperatively, postoperative complications according to Clavien-Dindo. |
| Study design: | Prospective controlled, observational, interrupted time series, monocentric study (before and after study). |
| Inclusion/Exclusion criteria: | Inclusion criteria : Patients undergoing elective or emergent laparotomy  Exclusion criteria : Preexisting surgical site infection |
| Measurements and procedures: | The control arm consists of 580 patients from the previous StOP?-study.  580 patients will be recruited in the trial arm.  Every patient has a follow up of thirty days in line with the recording of Swissnoso (national surveillance for SSI). |
| Study Intervention: | The wound closure will be done by a specialised team including one trained surgeon and one student. |

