# STUDY DESIGN

## General study design and justification of design

Prospective controlled, two armed, observational, monocentric study (before and after study).

To evaluate the impact of a specialised wound-closing team on surgical site infections

Included in the study are all patients (over 18 years, elective and emergency) with laparotomy and closure of the wound from Monday to Friday from 8:00 to 17:30 o’clock. We aim to include a total of 1785 participants.

The control group consists of the study population of the StOP?-study. In this population the wound closure was done by the same operation team under supervision of the main surgeon.

The screening of the first participant in the control group started on the 01.03.2016 and ended with the STOP? study on the 30.11.2016. The inclusion of patients in the intervention group takes place between 1.3.2017 and 30.11.2017. Therefore the end of data collection will be the 31.12.2017.

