## Assignment to study groups

The patients will be assigned to the study groups according to the time point of inclusion. In the period between 1.3.2016 to 30.11.2016 the control group was assessed. Patients operated between 1.3.2017 and 30.11.2017 represent the intervention group.

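### At the stated 720 laparotomies a year, nine months are expected to yield about 540 patients per period, which fits neither 580 per arm nor 36 points of 20 surgeries

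*Protocol*

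**What the plan says.** Section 10.2 of the protocol gives the basis for feasibility: "The average number of laparotomies from 8:00 AM to 5:30 PM from Monday to Friday per year are 720". This is the same weekday and daytime window that the eligibility criteria use. The next sentence sets the duration: "The study schedule includes first 9 months in the control (baseline: 2^nd^ arm of the STOP? Study) and then 9 months in the intervention group". The dates are fixed elsewhere. For the control group, section 7.3 says "In the period between 1.3.2016 to 30.11.2016 the control group was assessed"; for the intervention group, section 6.1 says "The inclusion of patients in the intervention group takes place between 1.3.2017 and 30.11.2017".

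The sample size, also in 10.2, is 484 evaluable surgeries per group for a reduction in SSI from 20% to 14% (5% significance, 80% power). It is then raised for loss: "In the ongoing StOP?-study we have a drop out and study refusal rate of maximal 20" per cent, and "Thus, a total of 1160 participants (580 per arm) need to be included". The synopsis repeats the target ("580 patients will be recruited in the trial arm") and describes the control arm as made up of 580 StOP? patients.

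Section 10.4.1 describes the primary analysis on a different scale: "An interrupted time series design will be used, including 36 data points (based on about 20 surgeries per data point) before" the intervention, and about 36 points of about 20 after it. Section 6.1 gives yet another total, 1785 participants.

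**The concern.** The annual volume and the nine-month schedule stand side by side in 10.2 as the grounds for believing that the target can be met, yet their product lies below that target. The series in 10.4.1 implies a third size per period, larger than both. The study has a single centre, and nothing in the protocol adds a site, extends accrual or gives a higher volume.

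Two things are at stake. The first is the power statement, which rests on 484 evaluable patients per group. The second is the layout of the primary analysis: someone following the protocol could not tell whether to build 36 short points or fewer points of 20, nor whether the intervention period ends on its date or at 580 patients. Settling either question once data are in hand would be a post hoc choice.

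**Working it through.** **The plan's own figure.** Pooled normal approximation without continuity correction, p1 = 0.20, p2 = 0.14, mean 0.17, difference 0.06:

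n = [z_α·√(2·0.17·0.83) + z_β·√(0.20·0.80 + 0.14·0.86)]² / 0.06² = [z_α·0.5312 + 0.8416·0.5295]² / 0.0036

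- One-sided 5% (z_α = 1.645): n = 484, which matches 10.2.
- Two-sided 5% (z_α = 1.960): n = 615.
- Inclusion target: 484 × 1.2 = 580.8, hence 580. Dividing by 0.8 gives 605.

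**Expected yield per period** (volume and duration from 10.2)

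- Before loss: 720 × 9/12 = 540. By calendar days, 720 × 275/365 = 542.
- At the maximal loss: 540 × 0.8 = 432.
- Against 580: 540/580 = 0.93, so 7% short before any loss. Signed general consent is an inclusion criterion (7.1), so refusals can only lower the 540.
- Against 484: 1 − 484/540 = 10.4%, the largest loss at which 540 eligible patients still give 484 evaluable.
- Volume at which nine months give 580 with no refusals: 580/0.75 = 773 a year.

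**The series** (10.4.1)

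- Surgeries needed per period: 36 × 20 = 720, equal to twelve months at the stated volume.
- Shortfall from nine months: 1 − 540/720 = 25% before loss; 1 − 432/720 = 40% at maximal loss.
- Against the inclusion target: 580/20 = 29 points, not 36.
- Points of 20 that can be filled: 540/20 = 27; 432/20 = 21.6, about 22.
- Surgeries per point if 36 points are kept: 540/36 = 15; 432/36 = 12.
- Volume needed for 720 in nine months: 720/0.75 = 960 a year.
- Both periods together: 2 × 720 = 1440, which equals neither 1160 nor 1785.

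**Two-proportion power**, Φ[(0.06·√n − z_α·0.5312)/0.5295]:

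| Evaluable per arm | One-sided | Two-sided |
| --- | --- | --- |
| 432 (540 less 20%) | 76% | 65% |
| 464 (580 less 20%) | 79% | 68% |
| 484 (required) | 80% | 70% |
| 540 (no loss) | 84% | 75% |

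The fall from 80% to 65% has separate causes. Moving from one-sided to two-sided at 484 costs about 10 points (80 to 70). Inflating by 1.2 leaves 464 after 20% loss and costs about 2 more (70 to 68). The accrual gap, 464 to 432, costs about 3 (68 to 65).

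**The case against.** The best defence is that the inputs are soft. The 720 is an average and the 20% a maximum, so 432 is a low end at average volume and not a forecast. With loss of 10.4% or less, 540 eligible patients still give 484 evaluable, and a year with about 7% more volume and no refusals would reach 580. This stands. A reader might infer that 580 cannot be reached and that the trial is bound to miss its evaluable number; the protocol supports only that 580 is not expected at the stated volume.

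The control arm may also be better off than the average suggests. The synopsis speaks of 580 control patients in a version dated 18.01.2017, after that period closed on 30.11.2016. If 580 is a real nine-month count, most of the accrual concern falls away. It may equally be the target restated, since 10.2 still calls StOP? ongoing. The protocol does not settle this.

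A reader might further take 65% power as the effect of slow accrual. It is not: two-sided power at the plan's own 484 is already 70%.

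Finally, one might conclude that the primary analysis is impossible. An interrupted time series can be run on 27 points of 20 or 36 points of 15, and the sample size was not derived from the series. What remains is that the stated layout is wrong. Words such as *about* do not cover a 25% gap before loss, and even a true 580 per arm would not fill 36 points of 20.

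**Conclusion.** The protocol contradicts its own figures. At the stated average volume, a nine-month period is expected to give about 540 patients before loss and 432 to 540 evaluable. That is 7% below the 580 to be included, and below 484 evaluable once loss exceeds about 10%. The series is the firmer part of the contradiction: about 720 surgeries per period fit neither nine months (25% to 40% short) nor 580 per arm.

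The conclusion assumes that 720 a year applies evenly to the March-to-November periods and that loss lies between 0% and 20%. For the control arm it is an inference from the average, because no count is identified as such. The power figures are for a simple comparison of two proportions, as in 10.2, and do not describe the power of the time-series model.

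**What to change.** State one consistent set of numbers in 10.2, 10.4.1, the English and German synopses, and 6.1 (where 1785 must be reconciled or removed):

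- the actual number of patients in the closed control period, saying whether the 580 in the synopsis is that count or a target;
- the expected intervention-period yield as a range, 432–540 evaluable;
- the matching two-proportion power: 76–84% one-sided, the sidedness under which 484 reproduces, or 65–75% two-sided, as the hypothesis of a change in either direction in 10.1 implies, naming which one applies;
- the series as about 22–27 points of 20 surgeries, or 36 points of 12–15;
- that the intervention period closes on its fixed date.

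The cost is protocol wording and a less favourable stated power. Closing the intervention period at 580 patients would cost more. At 60 a month it takes 580/60 = 9.7 months with no refusals, and at 48 a month, if the full 20% is lost before inclusion, 580/48 = 12.1 months. It can lengthen only the intervention period, because the control period is over, and it would end the match of calendar months between the two periods.

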| Risk-Benefit statement / GCP Statement: | SSI infections are associated with increased morbidity and length of hospital stay. Patients with SSI after laparotomy or laparoscopy typically need bed-side reopening of the skin or administration of antibiotic therapy. Thus, prevention of SSI is of high interest.  The primary treatment of the patient is not affected by the trial. The change of the surgical team potentially may irritate and distract other personnel that is involved in the treatment of the patient. This may be of relevance during the initial phase of the study. The operation time may rise a little. A higher risk for the patient is not to be expected as long as communication within the surgical team assures that all relevant information is passed to the closure team. Conversely, exchange of team members is frequently done in clinical routine for both surgeons and nurses.  This study will be conducted in compliance with the protocol, the current version of the Declaration of Helsinki, the ICH-GCP or ISO EN 14155 (as far as applicable) as well as all national legal and regulatory requirements. |

Studienzusammenfassung

| Sponsor / Sponsor-Investigator | [name], Department of Visceral Surgery and Medicine, Inselspital, Bern University hospital University of Bern, 3010 Bern |
| --- | --- |
| Titel: | Impact of a specialised wound-closing team on surgical site infections: A  prospective observational clinical trial |
| Abkürzung: | CLOT trial |
| Protokollversion: | Version: 1 Date: 18.01.2017 |
| Kategorie | Kategory A: Beobachtungsstudie. Die Behandlung der Patienten wird nicht verändert.. |
| Rationale | Wundinfekte sind eine häufige Komplikation nach abdominalchirurgischen Eingriffen. Der Wundverschluss erfolgt zu einem Zeitpunkt an welchem das chirurgische Team unter Umständen nach einer langen Operation müde und weniger konzentriert ist. Mit dieser Studie soll geprüft werden ob durch die Einführung von einem Wundverschlussteam die Rate an Wundinfekten gesenkt werden kann. |
| Ziel: | Prüfen ob die Inzidenz von Wundinfekten durch die Einführung eines Wundverschlussteams verändert wird. |
| Endpunkte: | Primärer Endpunkt: Wundinfekte 30 Tage postoperativ.  Sekundäre Endpunkte: Mortalität, Fasziendehiszenz, Komplikationen 30 Tage postoperativ. |
| Studiendesign: | Prospektiv kontrollierte Beobachtungsstudie (vorher – nachher Studie). |

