## Risks / Benefits

The primary treatment of the patient is not affected by the trial. The change of the surgical team potentially may irritate and distract other personnel that is involved in the treatment of the patient. This may be of relevance during the initial phase of the study. The operation time may rise a little, however, a higher risk for the patient is not to be expected. Conversely, exchange of team members is frequently done in clinical routine for both surgeons and nurses.

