## Other Outcomes of Interest

In order to perform subgroup analyses or adjusted analyses, the following variables are assessed (Dokument 1 Swissnoso):

- - Type of operation (Haupteingriff, Sekundäreingriff)
  - Grade of contamination (Kontaminationsgrad)
  - Duration of the procedure
  - Height and weight of the patient.

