### Assessment of other outcomes of interest

In order to perform subgroup analyses or adjusted analyses, following variables are assessed:

- Type of operation (primary, secondary surgery)
- Grade of contamination
- Duration of the procedure
- Height and weight of the patient
- Comorbidities

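### The primary model adjusts for total duration of surgery, which the team exchange can change, and omits body size and separately recorded comorbidity in a comparison of calendar periods

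*Protocol*

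**What the plan says.** Section 10.4.1 plans an interrupted time series and fixes its covariates: "We will include type of surgery, the NNIS-risk score (composed of ASA-score, wound contamination and duration of the surgery), as well as patient age". It gives their purpose as "Covariates are included to adjust for chance imbalances between baseline and post intervention groups". Section 10.4.2 uses the same set for the secondary outcomes.

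On duration, the risk-benefit statement in the synopsis says "The operation time may rise a little". Section 3.4 says "The operation time may rise a little, however, a higher risk for the patient is not to be expected". Under section 3.3 the second team closes the laparotomy, irrigates the wound and sutures the skin, so its work falls within the operation.

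On patient characteristics, section 5.3 says "In order to perform subgroup analyses or adjusted analyses, the following variables are assessed" and includes height and weight. The parallel list in section 9.1.3 opens with "In order to perform subgroup analyses or adjusted analyses, following variables are assessed" and contains "Height and weight of the patient" and also "Comorbidities", which section 5.3 does not list. None of these has its own term in the section 10.4.1 model.

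Section 6.2.1 states that there is no randomisation. Section 7.3 assigns patients by date: 1.3.2016 to 30.11.2016 for control, 1.3.2017 to 30.11.2017 for intervention.

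**The concern.** A covariate that the intervention can alter does not belong in a model for the total effect of that intervention without a check. Total duration includes closure. If the exchange adds minutes, there are two routes to distortion. If longer surgery itself raises the risk of infection, conditioning on duration removes that harm from the estimate. If the added minutes carry no risk, they still move some intervention patients into a higher NNIS class; the model then expects more infections from them than their condition warrants and credits the shortfall to the closure team. Both routes favour the intervention. If the second team closes faster, both reverse.

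The other half of the point is confounding. Groups formed by calendar period can differ for reasons other than chance, so the stated purpose of the covariates is too narrow. The time-series terms can absorb a gradual drift in case mix, but not a step that falls between the two periods, which are three months apart. Body size is wholly unadjusted. Comorbidity is adjusted only as far as the ASA-score reflects it.

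**Working it through.** **1. The protocol's own figure.** Section 10.2 gives 484 per arm for 20% against 14%, 5% significance and 80% power. With the pooled normal approximation and z = 1.645 (one-sided):

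n = [1.645·√(2·0.17·0.83) + 0.842·√(0.20·0.80 + 0.14·0.86)]² / 0.06² = (0.874 + 0.446)² / 0.0036 ≈ 484.

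This reproduces. (The two-sided version gives 615, which is a separate matter.) The calculation uses no covariates, so nothing below changes it.

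**2. Order of events.** ASA describes the patient, and contamination class is not a measure of closure time. Total duration ends after closure, hence after the exchange. Of the three NNIS components it is the one the protocol itself says the exchange may alter.

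**3. Illustration for duration.** The documents give no added minutes, no duration cut-off and no effect of duration on infection, so every input here is an assumption except the 20% and 14%. The set-up is a logistic model with 200,000 patients per period. Duration is gamma-distributed with mean 170 and SD 90 minutes, and a cut-off at 180 minutes puts about 39% of controls above it. Control SSI is 20%. The odds ratio within duration strata is (0.14/0.86)/(0.20/0.80) = 0.651. Long duration multiplies the odds of SSI by 1.5, 2 or 3, and the three values in each cell follow that order.

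| Added minutes | Intervention SSI, % | Total-effect OR | Duration-adjusted OR |
|---|---|---|---|
| 0 | 14.0 / 14.1 / 14.3 | 0.653 / 0.655 / 0.666 | 0.651 / 0.645 / 0.651 |
| 5 | 14.1 / 14.3 / 14.5 | 0.658 / 0.667 / 0.679 | 0.654 / 0.653 / 0.653 |
| 10 | 14.2 / 14.4 / 14.8 | 0.664 / 0.674 / 0.693 | 0.653 / 0.649 / 0.651 |
| 20 | 14.5 / 14.8 / 15.4 | 0.676 / 0.697 / 0.729 | 0.641 / 0.645 / 0.650 |
| 30 | 14.7 / 15.2 / 16.0 | 0.689 / 0.719 / 0.762 | 0.650 / 0.651 / 0.652 |

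Simulation error of the fitted odds ratio: √(1/40,000 + 1/160,000 + 1/28,000 + 1/172,000) = 0.0085 on the log scale, and 0.0085 × 0.65 ≈ 0.006. The small gap in the zero-minute row reflects this error and the non-collapsibility of the odds ratio.

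In risk terms, what the adjusted model hides is the rise over the zero-minute row. The smallest is 14.1 − 14.0 = 0.1 points (5 minutes, OR 1.5); the largest is 16.0 − 14.3 = 1.7 points (30 minutes, OR 3). The target difference is 6 points. The illustration covers only the first route (longer surgery raises risk) and adjusts for duration itself, whereas the NNIS score dilutes duration among three components.

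**4. Illustration for an omitted factor.** Assume a binary risk factor with 25% prevalence in controls, an odds ratio of 1.5 or 2, and a within-stratum OR of 0.651. The OR from the model without the factor is:

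| Prevalence difference, intervention minus control | Factor OR 1.5 | Factor OR 2 |
|---|---|---|
| +10 points | 0.691 | 0.699 |
| +5 points | 0.667 | 0.683 |
| −5 points | 0.646 | 0.623 |
| −10 points | 0.627 | 0.608 |

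With the factor in the model, the OR is 0.644 to 0.660 throughout. The omission can therefore push the estimate either way.

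**5. Room for more terms.** Expected SSIs at 484 per arm: 484 × 0.20 + 484 × 0.14 = 96.8 + 67.8 ≈ 165.

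**The case against.** The strongest reply is that duration is mostly accrued before closure and reflects how complex the case was. In a before-after study that is a legitimate confounder, and dropping it could add more bias than it removes. This stands, and it is why the remedy is to report both versions rather than delete duration. Time from incision to start of closure would separate the two roles, but nothing shows that it is recorded.

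It can also be said that the ASA-score covers comorbidity, that a short pre-specified set is defensible, and that sections 5.3 and 9.1.3 foresee further adjusted analyses. The first is partly right. The other two do not explain why variables collected for adjustment are absent from the only adjusted model described. Because section 10.4.1 fixes that list, it is not simply a detail left to the SAP.

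Several stronger readings are not supported:

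- A reader might infer that the protocol predicts longer operations and that the bias therefore favours the closure team. It says only that time may rise a little; with no change in duration there is essentially no distortion.
- A reader might attach a size, for instance by letting case mix shift expected SSI from 20% to 18%. With no true effect, an unadjusted two-sided test at 484 per arm would then reject about 12% of the time. The 2 points would be an assumption derived from neither feature of the model, and the planned analysis is an adjusted time series.
- A reader might take every candidate covariate as already in hand. Comorbidities are in section 9.1.3 only. Elective or emergency status appears as an eligibility descriptor and in no covariate list. The case report form is not shown.
- Contamination class should not be called a pre-incision variable; no section says so.

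**Conclusion.** The concern holds in this form. The protocol fixes a primary model, carried into the secondary analyses, that conditions on a quantity its own intervention may change. The same model leaves out body size, and comorbidity beyond the ASA-score, although both are collected for adjustment and allocation is by calendar period. The direction of the duration bias is conditional: towards the closure team if operations lengthen, against it if they shorten. Its size cannot be computed from the documents and may be small; the 0.1 to 1.7 points shown above rest wholly on assumed inputs. Confounding by the omitted variables can go either way. No stated figure in the protocol changes. The correction is worth making because it touches the primary estimate and costs little.

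**What to change.** In section 10.4.1, and through it section 10.4.2:

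- Add body mass index to the primary covariates and, where recorded in both periods, comorbidity. Add elective or emergency status only if it is confirmed as recorded in both periods.
- Enter ASA and wound contamination class as separate covariates, so that the duration component can be separated. If time from incision to start of closure is recorded in both periods, use it in place of total duration.
- Pre-specify and report the model with and without total duration (full NNIS score against ASA plus contamination), and say in advance which version carries the primary test.
- State that the covariates address confounding between periods, not only chance imbalance.

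The cost is protocol wording, a check of what the StOP? database holds for the control period, and a few more model terms. About 165 expected SSIs leave room for these if the model is fitted to individual patients; if it is fitted to the roughly 36 + 36 = 72 aggregated points, the added terms weigh more. The version without duration gives up some adjustment for case complexity, which is the reason to show both.
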